## Abstract

**Background:**

Lifestyle and habits, cardiovascular risk factors (CRF), bone and mental health, dietary habits, physical activity, among others are developed in childhood and adolescence. Family environment has shown to play an important role in these outcomes. However, whether the parent-child relationship lifestyle habits and health parameters can be influenced by physical activity patterns still unclear. The objective of this study will be to monitor and investigate the associations between lifestyle habits between parents and their children longitudinally, as well as verify whether in more active parents, the possible associations with lifestyle habits are different from those of parents considered less active.

**Methods:**

The sample will consist of parents (father, mother, or both) and their children /adolescents. The participants will be recruited through public call by flyers spread across all the regions of the city and also through social media. The health parameters will include cardiovascular (cardiac autonomic modulation, blood pressure and resting heart rate), bone mineral density, anthropometric indices, handgrip strength, mental health (quality of life, anxiety and depression symptoms and stress), self-reported morbidities and musculoskeletal pain. Lifestyle habits will include physical activity levels, sedentary behavior, sleep parameters, eating patterns, smoking and alcohol consumption. Sociodemographic variables of age, sex, ethnicity and socioeconomic status will be considered as covariates. The follow-up visits of data collection will be scheduled after a period of 12 months from the baseline assessment during every twelve months.

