### Sample

The sample for this longitudinal study will consist of adults and children and adolescents aged 6–17 years. The study will be carried out in the city of Presidente Prudente, located in the southeast region of Brazil and which has approximately 230,000 inhabitants according to information from the Brazilian Institute of Geography and Statistics.

Sample recruitment will take place through flyers spread across the five regions of the city (north, south, east, west and central area) and also through social media (Facebook, Instagram, Whatsapp, radio, TV) and researchers going to schools to extend the invitation. The inclusion criteria will be considered: i) children, adolescents and parents who do not have a pacemaker (as it can influence the results of the assessment of cardiac autonomic modulation, ii) who carry out all the assessments proposed by the study; iii) who have not used any type of caffeinated or alcoholic beverage in a period of 12 h before the assessments.

To calculate the sample, a correlation of 0.31 was used based on the study by Christofaro et al. [15] for the relationship between the physical activity of parents and children, considering a power of 80% and an alpha error of 5%. Anticipating possible sample loss, an additional 10% will be added to this calculation, totaling a minimum number of 176 participants. However, as multiple regressions will be carried out in the present study, the sample size was increased by 20%, totaling a final sample number of 212 participants to be evaluated (106 children and/or adolescents and at least one of their parents to be evaluated). The intention of the present study is to carry out reassessments every twelve months.

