### Statistical analysis

The sample characterization variables will be expressed as mean and standard deviation if the data are parametric and median and interquartile range if they are not parametric. The association between lifestyle habits, as well as direct health measures carried out between parents and children, will be analyzed using Linear Regression adjusted by age of adolescents and their parents, socioeconomic status, parents’ education. In the case of using categorical analyses, Binary Logistic Regression or Poisson (with robust variance adjustment) will be used. The statistical significance to be used will be 5% and the confidence interval will be 95%. The statistical package used will be SPSS version 25.0.

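### The article allows several members of one family into the analysis but names regressions with no family clustering, so standard errors will be too small wherever a family supplies more than one row to a model

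*Protocol article*

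**What the plan says.** On who enters, the Abstract (Methods) states: "The sample will consist of parents (father, mother, or both) and their children /adolescents". The Sample section plans "106 children and/or adolescents and at least one of their parents to be evaluated". Its inclusion criteria cover pacemakers, completion of the assessments, and caffeine or alcohol beforehand. They do not restrict a family to one child or one parent.

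On the analysis, the Statistical analysis section says that parent-child associations "will be analyzed using Linear Regression adjusted by age of adolescents and their parents, socioeconomic status" and parental education. For categorical outcomes, "Binary Logistic Regression or Poisson (with robust variance adjustment) will be used". No family effect, generalised estimating equation (GEE) or cluster is named. The section does not say whether a row is a child, a parent-child pair or something else. The robust variance is tied to the Poisson option and names no cluster.

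On size, the Sample section says "To calculate the sample, a correlation of 0.31 was used" for parent and child physical activity, with 80% power and 5% alpha, and then "an additional 10% will be added to this calculation, totaling a minimum number of 176 participants". A further 20% for multiple regression gives 212. Families are to be reassessed yearly.

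**The concern.** The models named assume independent rows, while the design admits families that can break this in two ways. If both parents take part and each is paired with the child in a separate row, the child's outcome appears twice. If siblings take part, they share a parent's value and their outcomes are likely to be correlated. Either way the model counts more information than the data hold. Standard errors are then too small, intervals too narrow and p-values too low.

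Resemblance within families is what the study sets out to measure, so zero within-family correlation is an awkward default. A robust variance used with Poisson regression for a binary outcome repairs the form of the variance. Unless it is computed over families, it does not deal with dependence between rows.

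**Working it through.** **1. The plan's own figure.** Inputs from the Sample section: r = 0.31, 80% power, 5% alpha (two-sided assumed; one-sided gives 64 pairs and does not fit).

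n = ((1.960 + 0.842) / atanh(0.31))² + 3 = (2.802 / 0.3205)² + 3 = 79.4, rounded up to 80 independent pairs.

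80 × 1.10 = 88 pairs = 176 people. 176 × 1.20 = 211.2, rounded up to 212 people = 106 pairs. Both stated figures reproduce. With 106 independent pairs the power at r = 0.31 is 90.2%.

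**2. Inputs that the article does not give.** These are the correlation between spouses (ρp), the residual correlation between siblings (ρc) and the share s of families bringing two children. Assumed ranges: correlations 0.2 to 0.5, s from 10% to 50%.

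**3. Variance inflation under no association.** With V the ratio of the true to the reported variance, the type I error is 2(1 − Φ(1.96/√V)).

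- One parent, one child per family: V = 1, type I error 5%.
- Two parents stacked against one child: the outcome is duplicated, so V = 1 + ρp. At 0.2, V = 1.2 gives 7.4%; at 0.3, V = 1.3 gives 8.6%; at 0.5, V = 1.5 gives 11.0%. If spouses are uncorrelated, V = 1.
- Two siblings sharing one parent in every family: V = 1 + ρc, hence the same 7.4% to 11.0%.
- Two parents by two children: V = (1 + ρp)(1 + ρc). Both at 0.2, V = 1.44 gives 10.2%; both at 0.5, V = 2.25 gives 19.1%.
- One parent, with a share s of families bringing two siblings: V = 1 + ρc × 2s/(1 + s). At s = 10%, ρc = 0.2, V = 1.036 gives 5.4%. At s = 50%, ρc = 0.5, V = 1.333 gives 9.0%.

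**4. Simulation check.** Ordinary least squares on stacked pairs under no association, 4,000 runs per scenario (Monte Carlo standard error about 0.3 to 0.6 percentage points), correlations 0.2 to 0.5:

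| Layout | Rows | True SE / reported SE | Type I error, ordinary SE | Type I error, family-clustered SE |
|---|---|---|---|---|
| 106 families, 1 parent × 1 child | 106 | 0.99–1.03 | 4.7–5.2% | 5.5–5.9% |
| 53 families, 2 parents × 1 child | 106 | 1.10–1.25 | 7.5–11.8% | 6.1–6.8% |
| 106 families, 2 parents × 1 child | 212 | 1.08–1.20 | 6.8–10.2% | 4.9–5.9% |
| 53 families, 1 parent × 2 children | 106 | 1.09–1.24 | 7.3–11.0% | 6.3–7.0% |
| 53 families, 2 parents × 2 children | 212 | 1.21–1.51 | 10.4–18.3% | 5.7–6.9% |

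The simulation agrees with the formulas. Clustering on family removes most of the excess, and the small remainder reflects the modest number of families.

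**5. Effect on power.** In the sibling mix of step 3, the effective number of children is 106/V, from 102 in the mildest case to 80 (106/1.333 = 79.5) in the heaviest. At about 80, power for r = 0.31 is still about 80%.

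**The case against.** The strongest reply is that the article never says pairs are stacked. Adjusting for the ages of the child and the parents fits one row per child equally well, with mother and father in separate models or as separate predictors. In that layout a second parent creates no duplicate outcome and no inflation. Nor does any section say that siblings will be enrolled; that is inferred from the lack of a limit. The sample size is built on 106 child-parent pairs, and one pair per family is harmless. Finally, this is a condensed article: the cluster variable and the variance estimator are often fixed in a fuller document, and naming a model class does not exclude clustered standard errors.

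Most of this stands, and it makes the point conditional. A reader might infer that the standard errors of every planned association are wrong, or that the Poisson variance is certainly unclustered. The article supports neither: it gives no unit of analysis and is silent on the cluster.

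What the reply does not remove is the mismatch. Entry of both parents is explicit, and the analysis section commits to models that assume independence when run as named. An analyst could follow that section to the letter, stack the pairs and report intervals that are too narrow.

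**Conclusion.** The point holds in conditional form. Where a family contributes more than one row to a model, the regressions as named will understate standard errors and p-values under positive within-family correlation. Where each family contributes one row, they will not.

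For assumed correlations of 0.2 to 0.5, type I error at nominal 5% is about 5.4% to 9% when 10% to 50% of families bring two siblings, about 7.5% to 12% when two parents are stacked per child (53 families; somewhat less with 106), and about 10% to 18% for two parents by two children. The direction is the same throughout. The size cannot be fixed from the article, because both the correlations and the family mix are assumptions.

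A reader might also conclude that 212 is too few. That is not shown: the figure reproduces, and even the heaviest sibling mix considered leaves power near 80%. This should be settled before analysis, but it does not undermine the design.

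**What to change.** In the Statistical analysis section, state the unit of analysis and adopt one of two layouts:

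- (a) One row per child, with mother's and father's values in separate models or as separate predictors. Cluster standard errors on family if siblings are enrolled.
- (b) One row per parent-child pair, with parent sex in the model and GEE, a mixed model or cluster-robust variance by family, for the linear, logistic and Poisson models alike.

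In either case, say that any robust variance is clustered on family, and let the same family-level clustering cover the annual reassessments, which add further rows per family. The count of 106 children need not be redefined.

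The cost is a family identifier in the data set, a few sentences of text and slightly wider intervals.

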**Discussion:**

The family environment has great potential to determine lifestyle habits in children and adolescents. Based on the results presented in the present study, we hope that health promotion actions can be better designed in the family environment.

**Table Tab1:** 

Text box 1: Contribution to the literature
• There is limited evidence from longitudinal studies on how parents’ lifestyle habits can influence those of their children, especially in developing countries.
• The present study will analyze the role of physical activity in different domains and intensities in lifestyle habits among parents and their children.
• Our expectation is that health promotion actions can be better directed in the family environment with the future findings of this study.

## Introduction

Childhood and adolescence are important periods in a human being’s life, as many characteristics and lifestyle habits acquired at these stages of life have a higher chance of being carried into adulthood. Among these characteristics and habits, body composition [1], cardiovascular health variables such as blood pressure and resting heart rate [2], eating habits [3], sleep time and quality [4], mental health [5], sedentary behavior [6], physical activity [7], among others.

One factor that has shown to influence the lifestyle habits of children and adolescents is the behavior of their parents. Studies have shown relationships between parents and their children regarding obesity [8], bone health [9], hypertension [10], eating habits [11], mental health [12], sleep [13], sedentary lifestyle [14] and physical activity [15, 16]. Parents generally serve as an example and are the ones who provide social support for important habits such as eating and physical activity.

In relation to this topic, a gap that requires investigation in the existing literature is whether the physical activity levels of parents can impact various domains of their children’s lifestyle and health. Specifically, it is important to explore whether physical activity conducted in different domains (such as occupational physical activity, leisure-time sports, and commuting activities) and intensities (light, moderate, vigorous) can influence these relationships. In addition, the cross-sectional design of previous studies is a limitation in the current literature [10, 13, 15], which prevents the inference of causality, and the information derived in studies from developing countries such as Brazil is another gap, as most of the information available in the literature were obtained in developed countries [8, 17].

Therefore, the objective of this study will be to monitor and investigate the associations between lifestyle habits between parents and their children longitudinally, as well as verify whether in more active parents, the possible associations with lifestyle habits are different from those of parents considered less active. Our hypothesis is that lifestyle characteristics and habits between parents and children are positively associated in more active parents.

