## Discussion

This research project will aim to verify the influence of parents’ health characteristics and lifestyle habits on their children. To this end, children and adolescents aged 6–17 and their parents will be assessed. Such information will be important, since lifestyle habits developed in childhood and adolescence tend to persist into adulthood [1, 3].

The family environment tends to guide the lifestyle habits of young people, and the current study will monitor participating families longitudinally. Among the important lifestyle habits to be monitored, we highlight physical activity. Christofaro et al. [16], in a study that evaluated the relationship between physical activity carried out by parents currently and also in the parents’ own childhood and adolescence, observed that the practice of physical activity among parents was positively associated with the practice of physical activity in their children.

In addition to the lifestyle habits between parents and their children we will also explore the possible role that physical activity in the associations. A main novelty will be to consider the possible role of physical activity in its different domains, analyzing occupational physical activity (work or housework for parents and physical activity at school for children), leisure-time sports and commuting actives. This project will also consider the role of different intensities of physical activity (light, moderate and vigorous) in the associations of lifestyle habits of parents and children.

Children, adolescents and active adults are less likely to be affected by cardiovascular diseases, for example, which are responsible for the highest causes of death in the world [20]. In the short term, this study could provide important information about the family environment in which health promotion strategies can be created. One of the answers we are aiming to obtain is if different types of physical activity and different types of intensity will have the same role between the associations of parents’ and children’s habits, or it will be different. With these estimates, for example, it will be possible to identify where health promotion actions should be prioritized for the population investigated.

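### The objective compares parent-child associations between more and less active parents, but the hypothesis covers one group only and the stated regression has no term for the comparison

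*Protocol article*

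**What the plan says.** The aim in the Abstract (Background), repeated in the Introduction, is comparative: to "verify whether in more active parents, the possible associations with lifestyle habits are different from those of parents considered less active". The Introduction then gives the hypothesis: "Our hypothesis is that lifestyle characteristics and habits between parents and children are positively associated in more active parents". Less active parents do not appear in it.

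The Discussion returns to the subject, saying that "we will also explore the possible role that physical activity in the associations", and presents the role of activity in its different domains as a main novelty of the project.

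The Statistical analysis section gives the models. Associations between parents and children "will be analyzed using Linear Regression adjusted by age of adolescents and their parents, socioeconomic status, parents’ education". For categorical outcomes: "In the case of using categorical analyses, Binary Logistic Regression or Poisson (with robust variance adjustment) will be used". No moderator, product term, comparison of slopes or stratification is mentioned.

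In the Sample section, "a correlation of 0.31 was used" for the relationship between parents' and children's activity, with 80% power and 5% alpha. This leads to 176 and then 212 participants, that is, 106 children with at least one parent each.

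**The concern.** Three statements that should describe one question describe two. The objective asks whether an association differs between groups of parents. The hypothesis asks whether an association exists in one of those groups. The model estimates a single association across all parents.

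The hypothesis could be true with identical associations in both groups, so confirming it would not meet the objective. A regression of the child's value on the parent's value plus covariates returns one slope averaged over parental activity, which says nothing about how that slope varies. Followed as written, the plan leaves open the question that the Discussion presents as its novelty and from which it hopes to identify where health promotion should be prioritised.

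**Working it through.** **1. Objective, hypothesis and model side by side**

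| Element | Where | Quantity addressed |
|---|---|---|
| Objective | Abstract; Introduction | Slope in more active parents minus slope in less active parents |
| Hypothesis | Introduction | Slope in more active parents is above zero |
| Model | Statistical analysis | One slope over all parents, adjusted |
| Sample size | Sample | One correlation over all pairs |

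Only the first row is a difference.

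**2. The plan's own sample size.** Inputs from the Sample section: r = 0.31, power 80%, alpha 5% (taken as two-sided), 10% for loss, 20% for multiple regression. With Fisher's z, atanh(0.31) = 0.3205:

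n = ((1.960 + 0.842) / 0.3205)² + 3 = 79.4, so 80 pairs.

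80 × 1.10 = 88 pairs = 176 participants. 88 × 1.20 = 105.6, so 106 pairs = 212 participants.

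Both stated figures reproduce. With all 106 pairs, power for r = 0.31 is Φ(0.3205 × √103 − 1.960) = Φ(1.29) = 90%. The calculation is right for the overall correlation.

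**3. Power for the comparison, two groups.** The document gives no group sizes and no group-specific correlations, so these are assumptions: 53 pairs per group, independent pairs, no covariates, one wave, two-sided 5%.

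SE of the difference in z = √(1/50 + 1/50) = 0.200.

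For 0.31 versus 0: 0.3205 / 0.200 = 1.60, and power = Φ(1.60 − 1.96) = 36%.

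The result depends heavily on the assumed contrast:

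| Correlations assumed | Power, 53/53 | Total pairs for 80% power |
|---|---|---|
| 0.31 vs 0 | 36% | 312 |
| 0.45 vs 0.15 | 39% | 290 |
| 0.41 vs 0.21 | 20% | 642 |
| 0.50 vs 0.10 | 61% | 162 |

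The difference detectable with 80% power is (1.960 + 0.842) × 0.200 = 0.560 on the z scale, about 0.51 versus 0.

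**4. Power for the comparison, continuous moderator.** By simulation, with a normal moderator, a slope that changes linearly with it, and an average slope of 0.31 in the upper half and 0 in the lower half:

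| Pairs | Continuous product term | Median-split product term |
|---|---|---|
| 106 | 51% | 36% |
| 95 (10% loss) | 45% | 32% |

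**5. Why separate p-values would not substitute, if parents were split.** Suppose r = 0.31 in both groups, so there is no difference. Power within 53 pairs is Φ(0.3205 × √50 − 1.960) = Φ(0.31) = 62%. The chance that exactly one group is significant is 2 × 0.62 × 0.38 = 47%, half of it (24%) with the active group the significant one. With splits of 48/48 and 35/71 the discordance is 49% and 53%. A direct test of the difference would err 5% of the time.

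**The case against.** The Statistical analysis section is one paragraph in a journal article. It names a regression family and covariates, and does not say that product terms are excluded. A fuller plan, not shown, may well specify an interaction and a definition of more active. The role of activity is described as something to explore in an observational cohort, and the sample size text ties the 0.31 to the overall relationship without claiming power for moderation.

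Much of this stands. The Sample section makes no false power claim. How activity is scaled or cut could properly sit in an analysis plan, and the choice between continuous and grouped activity is partly preference. What does not go away is the mismatch in the text itself: the hypothesis does not express the stated objective, and an interaction added elsewhere would leave that wording unchanged.

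Three stronger readings are tempting, and the document does not support them.

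- A reader might infer from the one-group hypothesis that the investigators will split parents and treat significance in one half as a difference. No section prescribes a split or subgroup p-values. The 47% and 24% describe a hypothetical procedure, not a stated rule.
- A reader might take about one third as the power for the interaction. That figure belongs to a dichotomised comparison of 0.31 versus 0. The same contrast with a continuous moderator gives about 50%, and other contrasts with two groups give 20% to 61%.
- A reader might expect a split on parental activity to bias the result when activity is itself the exposure. Restricting the range lowers the correlation within each half, to about 0.19 under normality with a median split. The planned method is regression, and the slope is unaffected by that restriction. The loss is in precision.

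**Conclusion.** The point holds as a mismatch between objective, hypothesis and model. As written, the plan estimates one overall parent-child association, and its hypothesis could be confirmed with no difference between more and less active parents.

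The sample size is correct for its own purpose and should not be read as covering the comparison. Power for the comparison is probably limited, but its size is conditional: the figures rest on assumed correlations, an assumed split or a linear normal moderator, independent pairs, no covariates and a single wave. Annual reassessments, or more than one parent per child, would change them.

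**What to change.** 1. **Introduction.** Word the hypothesis as a difference: the parent-child association is stronger in more active than in less active parents.
2. **Statistical analysis.** Add parental physical activity and the product of parent habit and parental physical activity to the model, preferably with activity continuous. If groups are kept, fix the measure and cut-point in advance. Report the product term with its 95% CI, and state that no difference will be claimed from separate subgroup p-values.
3. **Where parental activity is itself the exposure.** Use a different activity domain as the modifier, or a curvature term.
4. **Sample.** Add that the calculation covers the overall correlation of 0.31 only. Label the moderation analysis exploratory with limited power. Give any power figure with its assumptions, for example about 36% (median split) or about 50% (continuous moderator) for 0.31 versus 0 with 106 pairs.

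The cost is some rewording, one further model term beyond the activity main effect, and a less favourable stated power for this objective. No new data are needed.
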